## Abstract

**Background:**

Smoking is one of the most avoidable health risk factors, and yet the quitting success rates are low. The usage of tailored health messages to support quitting has been proved to increase quitting success rates. Technology can provide convenient means to deliver tailored health messages. Health recommender systems are information-filtering algorithms that can choose the most relevant health-related items—for instance, motivational messages aimed at smoking cessation—for each user based on his or her profile. The goals of this study are to analyze the perceived quality of an mHealth recommender system aimed at smoking cessation, and to assess the level of engagement with the messages delivered to users via this medium.

**Methods:**

Patients participating in a smoking cessation program will be provided with a mobile app to receive tailored motivational health messages selected by a health recommender system, based on their profile retrieved from an electronic health record as the initial knowledge source. Patients’ feedback on the messages and their interactions with the app will be analyzed and evaluated following an observational prospective methodology to a) assess the perceived quality of the mobile-based health recommender system and the messages, using the precision and time-to-read metrics and an 18-item questionnaire delivered to all patients who complete the program, and b) measure patient engagement with the mobile-based health recommender system using aggregated data analytic metrics like session frequency and, to determine the individual-level engagement, the rate of read messages for each user. This paper details the implementation and evaluation protocol that will be followed.

**Discussion:**

This study will explore whether a health recommender system algorithm integrated with an electronic health record can predict which tailored motivational health messages patients would prefer and consider to be of a good quality, encouraging them to engage with the system. The outcomes of this study will help future researchers design better tailored motivational message-sending recommender systems for smoking cessation to increase patient engagement, reduce attrition, and, as a result, increase the rates of smoking cessation.

**Trial registration:**

The trial was registered at clinicaltrials.org under the ClinicalTrials.gov identifier NCT03206619 on July 2nd 2017. Retrospectively registered.

## Background

New technologies such as smartphones and wearables can be used to support behavior change among patients, as many studies have already shown [1–7]. One of the ways in which technology is used to do so is by designing tailored health messages targeted at patients. Some such platforms use expert systems [8] that use the rules of human expert reasoning and infer results based on people’s answers to questions about behavior knowledge and motivational aspects like attitude and self-efficacy. Yet another type of system is a recommender system, which aims at sending messages tailored to users’ preferences [9–11]. These platforms employ algorithms to predict which message is most similar to its users’ previously preferred messages.

A recommender system is a piece of software that learns to predict the best item for each user from a set of items [12]. Items can be text messages, movies, books, people, or anything else that can be recommended. Recommender systems have been exploited most extensively in the spheres of e-commerce and leisure, through the recommendation of, for instance, movies, books, and music [13]. For example, if a system knows the books you have liked in the past, it aims to forecast the books you may also like in the future. This can be done using different techniques like comparing the features of the books you have liked with the features of other books you have not read, as shown in Fig. 1, or by considering books that people with similar tastes as you have also liked.

**Fig. 1 Fig1:**
[figure not shown]
Concept diagram of a simple recommender system. In this example, the recommended items are books. The user receives suggestions on what to read next based on the genres and features of books he or she has liked in the

Recommender systems have also been used in the healthcare domain. Health recommender systems are especially aimed at providing feedback and recommendations on health status and heath behaviors, such as lifestyle, nutrition [14], obesity [15], diabetes [16, 17], drug side effects [18], and smoking cessation [19]. The type of feedback is based on algorithms predicting the type of message needed on the basis of previously measured variables. The required input can be taken from electronic health records as described by Wiesner et al. [20] or may be based on a person’s interest in specific leisure-time behaviors.

However, few studies use this technique, and their potential is still to be exploited [21–23]. In addition, health recommender systems need to be precise and accurate in order to be effective. That optimization can already be found in recommender systems used for ecommerce and leisure. However, assessing the quality of health recommender systems in terms of appreciation of the recommendations by patients and their behavioral effects has so far not been explored in-depth. This can be done using experimental designs aimed at measuring their objective accuracy [24] or by finding out their users’ subjective opinions as described in the ResQue framework [25]. The goal of this study is develop and evaluate the quality of a health recommender system to fill this existing gap.

The health recommender system chosen for the study is aimed at supporting smoking cessation, because smoking is directly associated with a number of diseases: chronic obstructive pulmonary disease, asthma exacerbation, cataracts, pulmonary fibrosis, oral cavity cancer, pharynx cancer, larynx cancer, esophagus cancer, lung cancer, and bladder cancer, among others [26]. Consequently, quitting smoking is the most important decision smokers can take to optimize their chances to reduce health risks and increase the longevity of their lives [27]. Several studies explored the effects of innovative tailored behavioral change methods for smoking cessation and demonstrated that they can contribute to a higher success rates [28–30]. Other studies showed that the delivery of tailored motivational messages using mobile phones as a platform could be an effective way to enable smoking cessation [31–35] as well as to impact other aspects of health, such as promoting physical activity and exercise [36, 37], mental healthcare [38], and alcohol-related harm [39], among others. These tailored messages are usually pieces of text based on the user’s responses to certain questions, assessing their attitude, social support, self-efficacy, and type of action planning.

Yet, quitting smoking is often accompanied by several barriers, such as nicotine abstinence syndrome that may have consequences like headaches, cravings, intestinal disorders, weight gain, insomnia, restlessness, nervousness, depression, and irritability, among others [40, 41]. As a consequence, the rate of smoking relapses is high and success rates are often low [42–46], illustrating a clear need for providing messages that are highly personalized and tailored to the needs of each person at that point in time. Health recommender systems may have specific added value here as they use algorithms to optimally choose not only the type of message to be sent but also when it is sent.

In the current study, we will combine the principles of tailoring with two recommender systems, which customize messages and predict the best time to send the tailored motivational health messages to a cohort of patients who are trying to quit smoking using a mobile app. To select the most relevant message topic that can foster healthier habits in each patient, a health recommendation system algorithm (HRSA) accesses each patient’s personal health records and feeds the algorithm with this health data. Since the messages are delivered using smartphones and are tailored as per each patient’s health data, we call our system an mHealth Recommender System (m-HRS).

Wendel et al. [47] suggested four basic requirements to reduce potential barriers to using recommender systems: 1. Effort input minimization to reduce users’ burden; 2. Privacy assurance; 3. Optimizing message usefulness; and 4. Enjoyment.

The quality of the system is strongly associated to the patients’ attitudes toward the system and, consequently, to its usage [48]. A health system that patients feel is not of a good quality and one they cannot trust will not be used [49]. By increasing the perceived quality of the system, patients will be encouraged to adopt the system and use it more, which will lead to better health outcomes [50, 51].

Attrition is a well-known problem in digital healthcare interventions [52]. It is important to increase appreciation and thus raise patient engagement, thereby keeping attrition to a minimum. This is especially relevant in m-HRS because the more user engagement with the system, the more the system learns about the user, and, consequently, the stronger the system becomes. Alkhaldi et al. explained the importance of user engagement in digital health interventions [53]. Although there are different definitions of engagement, the one used in this study was proposed by Alkhaldi et al. in the study “Users revisiting the digital intervention”. A high engagement in digital health interventions is also associated with better patient health outcomes [54, 55]. This is because engaged patients read more tailored motivational health messages and therefore receive more such prompts. This has a positive impact on their behavior change, such as quitting smoking, as some studies have already shown [56, 57]. However, the novelty effect may also influence their attrition. Consequently, it would be necessary to compare how patients’ opinions regarding the HRS messages evolve throughout the intervention.

In conclusion, the first goal of this study is to describe the patients’ perceived quality of the m-HRS. The second goal is to assess the patients’ level of engagement with the messages generated by the system. Identifying which system features and user characteristics determine differences in user engagement and quality perception may help improve the design of future m-HRS platforms.

## Methods/Design

### Participants

For this observational prospective study, we will analyze patients participating in the SmokeFreeBrain project [58] for a period of 12 months.

The inclusion criteria for the study are patients who are attending the smoking cessation program Smoke Free Brain [59, 60] at the Virgen del Rocio University Hospital, are at least 18 years old, are willing to start treatment to quit smoking, own an Android smartphone and know how to use it, have installed the smoking cessation app recommended by the doctor, and who have not previously had any known adverse effects to the pharmacological treatment.

### Trial design

Patients will be provided with a purpose-built Android-based mobile application that allows them to receive messages and rate them on their smartphones. The app is called “Libre de humos”, or “Smokefree” in English. From here onward, we will refer to it as “the app”. The app’s other features include a goal achievement dashboard, physical exercise records, a relapse diary, a relaxation tool, mini-games to help patients overcome cravings through distractions—one of which is based on the webFitForAll exergaming platform protocol [61, 62]—and an informative section with content on various topics related to smoking cessation.

As no formal methodology has yet been used to assess mobile health recommender systems, we will use the message ratings, patients’ app usage behavior, and an adapted set of questions for the patients to compare their levels of quality appreciation and engagement. This will allow us to compare differences between the m-HRS patients’ opinions over time.

### App features and clinical integration

The present study will focus on exploiting features of smartphones that allow users to receive messages from a server and track their activity and interaction. The app can connect with the smoking cessation unit of the hospital’s electronic health record using Mirth Connect software. It interconnects the following:The hospital user database to access the patients’ demographic dataThe hospital clinical data base to access the patients’ clinical informationThe Lightweight Directory Access Protocol to validate the credentials of the healthcare professionals who access the hospital system

The information requested by the app is processed and selected from the electronic health record database, formatted using the ISO13606 standard, and sent back by the Mirth Connect platform.

Therefore, all the information regarding a patient’s profile—name, age, gender, date of quitting smoking, type of pharmacological treatment—is automatically loaded in the app without patients needing to input anything apart from a code provided by their clinicians. Furthermore, using the clinical station—the system interface at the hospital—healthcare professionals can monitor the patients’ activity using the app. For instance, if a patient logs a relapse, his or her doctors will be able to access it, provided they have the patient’s consent to do so.

The app will allow patients to rate the messages they have received using buttons to “Like” (positive), “Dislike” (negative), or “Don’t mind” (neutral), as shown in Fig. 2. The messages they will receive fall under one of the following five topics: general motivation, diet tips, physical exercise tips, personal performance, and the benefits of being a non-smoker.

**Fig. 2 Fig2:**
[figure not shown]
Screen captures of the message list and the rating mechanism of the “Libre de humos” smoking cessation app. Patients can provide feedback on the messages they receive via the app. They can provide feedback on each message by indicating “like”, “dislike”, or “indifferent”

Each of these topics has a pool of 150 different messages, along with useful tailored information for the patients. These topics and messages have been approved by a smoking cessation psychologist as well as a pulmonologist from the hospital.

Thus, this design will show whether patients prefer the messages selected by the m-HRS at the end of the pilot as a consequence of the HRSA being trained to better match the patient’s preferences, as opposed to the messages sent at the beginning when the HRSA was not configured to learn and improve messages based on the patients’ feedback.

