#### Sending the messages

The frequency at which patients will receive messages is based on the conclusions of Abroms et al. [67] considered in combination with the transtheoretical behavior change model [68]. This model was chosen because the counseling offered at the hospital’s smoking cessation unit is partially based on it, and we wanted the messages to be in line with this counseling. We started considering patients in the preparation phase, which is when they can join the program.Preparation: One message a day until the day of quitting—the topic of these messages is not predicted by the HRSA but chosen at random, and they cannot be rated, so they have no influence on the HRSAAction: Four messages on the day of quitting, and one message a day for the following week.Maintenance: Three messages a week after that, for one year.

In the maintenance phase, as per the transtheoretical behavioral change model, the messages will be sent at random days during the week. In total, a patient who completes the yearlong treatment will receive a total of 150 messages from the m-HRS. The time at which the messages will be sent is also calculated by the HRSA, based on the time difference between when a message is sent and when it is read. The day will be divided in 12 two-hour periods during which the message can be sent at any random time. The sooner the patient reads the message after receipt, the more likely it is that the next message will be sent in the same two-hour period. Patients can deactivate messages during a specific period of time through a do-not-disturb setting. Just like the final decision of the message topic, the messages’ timing is also based on a probability vector.

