### Quality

#### Objective quality

Since the HRSA predicts the message topic and timing of delivery, the objective perceived quality will be measured using two metrics: the precision of the message topics, and how long after receiving the message the users read it.

The precision metric is defined as the relation between the number of hits per message in the first month (baseline) and the extent of “positive”, “neutral”, and “negative” feedback per message in month 3, month 6, month 9, and month 12. Hits are messages with only positive feedback (1) Precision_p_ and with both positive and neutral feedback (2) Precision_p&n_.

1$$ Precisio{n}_P=\frac{\mid \mathrm{m} essages\ with\ positive\ feedback\mid }{\mid all\  messages\ with\  any\  feedback\mid } $$
2$$ Precisio{n}_{p\&n}=\frac{\mid messages\ with\ positive\ and\ neutral\ feedback\mid }{\mid all\  messages\ with\  any\  feedback\mid } $$

We expect the acceptance rate to be higher in month 12, as compared to the previous months, as by this time the HRSA will have more patients and enough information to make accurate decisions.

We will calculate the precision of the system at different points of time, which will reflect the users’ feedback and their interactions with specific sections of the app. All this information is stored in the database of the m-HRS.

The time-to-read metric is defined as the time difference between when the message was sent and when it was read by the user. We will use it to assess the evolution in the quality of the HRSA to predict the best time at which to send a user messages—we theorize that the lesser the time-to-read, the better it is for the user to receive messages at that time.

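### The protocol says the design will show an effect of training the recommender algorithm, but a single cohort compared over time cannot isolate that effect, and the untrained comparator it names is not available as described

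*Protocol article*

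**What the plan says.** All references are to the protocol article.

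- **The claim.** App features and clinical integration, in the text after Fig. 2, promises that the design can establish a preference for "messages selected by the m-HRS at the end of the pilot as a consequence of the HRSA being trained". The comparator is the messages sent "at the beginning when the HRSA was not configured to learn and improve messages" from patients' feedback.
- **The design.** Participants: "For this observational prospective study, we will analyze patients participating in the SmokeFreeBrain project". Trial design says the measures will allow the authors to "compare differences between the m-HRS patients’ opinions over time". No control group and no concurrent set of non-algorithm messages is described.
- **The metric.** Objective quality takes the first month as baseline and compares it with months 3, 6, 9 and 12. Precision is the share of hits among messages that received any feedback. A higher acceptance rate is expected in month 12, and the reason given is that the algorithm will by then have more patients and more information.
- **The random-topic messages.** Sending the messages says of the preparation phase: "the topic of these messages is not predicted by the HRSA but chosen at random, and they cannot be rated".
- **The algorithm's inputs.** Choosing the message topic lists demographic similarity, perceived utility (ratings and app visits) and stated initial interest. It gives no date from which ratings begin to count.
- **The probability vector.** Sending the messages says that message timing, "Just like the final decision of the message topic", is based on a probability vector.
- **Dropout.** Sample size expects 50%.

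**The concern.** The sentence attributes a preference to one cause, the training of the algorithm. To support that, the data must show what the same patients would have thought of messages from an untrained algorithm at the same time. The design offers only earlier against later. Between the two, patients move further from their quit day, some leave, and some stop rating.

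The protocol names several of these rival explanations itself. Background says novelty may influence attrition. Discussion lists removal of the app after quitting, after relapse or through never engaging. Limitations says the algorithm cannot distinguish changes of interest during cessation. None of these passages withdraws the causal sentence.

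Perceived quality is a primary outcome, and precision is one of its two objective metrics. If precision rises, the sentence invites the reader to credit the algorithm. If it falls or stays flat, it invites the conclusion that training did not work. Neither inference would be sound.

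**Working it through.** **1. The plan's own figure.** Sample size: 120 × (1 − 0.50) = 60 completers, and 60 × 150 = 9,000 messages. This reproduces. No power calculation exists to check. The question here is whether the effect can be identified, and more messages would not change that.

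**2. Is the named comparator available?** There are two readings of the beginning.

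- *Preparation phase.* Topics are random and outside the algorithm, but the messages cannot be rated. Precision counts only messages with feedback, so none of them can enter it.
- *Month 1.* This is the stated baseline and it is rated. However, no section describes a period after quit day in which learning from ratings is switched off. Whether month 1 is untrained in the sense the claim needs is therefore not established.

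**3. Dropout alone, with no learning.** Assumptions: each patient's like-rate is constant, half the patients drop out before month 12, and rating volume is equal. Write c for the like-rate of completers and d for that of dropouts.

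Month 1 precision = 0.5c + 0.5d. Month 12 precision = c. Change = 0.5(c − d).

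| c / d (assumed) | Month 1 | Month 12 | Change (points) |
|---|---|---|---|
| 50% / 50% | 50% | 50% | 0 |
| 55% / 45% | 50% | 55% | +5 |
| 60% / 40% | 50% | 60% | +10 |
| 70% / 30% | 50% | 70% | +20 |
| 45% / 55% | 50% | 45% | −5 |

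In completers only, month 1 and month 12 are both c, so the change is 0 in every row. A same-patient contrast removes this component.

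**4. Selective rating, with no dropout and no learning.** Suppose 50% of messages are liked, and the chance of rating a message that is not liked falls to a fraction f of its month-1 value. Precision becomes 0.5 / (0.5 + 0.5f): 56% for f = 0.8, 63% for f = 0.6 and 71% for f = 0.4. A same-patient contrast does not remove this.

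**5. Masking.** A true gain of 10 points from learning, with an assumed novelty decline of 10 points, shows as 0.

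**6. Could the probability vector help?** If the topic is drawn with probabilities p over five topics, ratings can be reweighted to uniform choice with weights 0.2/p. The effective share of messages is 1 / (0.04 × Σ 1/p).

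| Assumed vector | Σ 1/p | Effective share |
|---|---|---|
| 0.4, 0.3, 0.1, 0.1, 0.1 | 35.83 | 70% |
| 0.8, four at 0.05 | 81.25 | 31% |
| 0.9, four at 0.025 | 161.11 | 16% |

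Growth of the gap between algorithm and uniform choice can also come from dropout. Suppose the vector is fixed, completers have a gap of 9 points and dropouts have none. The pooled gap is then 0.5 × 9 + 0.5 × 0 = 4.5 points in month 1 and 9 points in month 12, with no learning.

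**The case against.** The strongest reply is that this is one sentence in a section on app features, not an objective. The goals in Background are to describe perceived quality and to assess engagement. The study is labelled observational, and Discussion warns that the metrics must be analysed carefully to avoid simplistic conclusions. This stands in part. The descriptive goals need no concurrent comparator and are sound. But a general caution does not retract a specific causal claim, and the reason given under Objective quality for expecting a better month 12 repeats the attribution.

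Several stronger readings are tempting, and the protocol does not support them:

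- *Month 1 is already a trained state, because the algorithm uses demographics and stated interests from the start.* The claim concerns learning from patients' feedback. Demographics and stated interests are not message feedback, so using them early does not contradict it. Early use of ratings would, but no start date is given. The text is unclear on this point and does not show the claim to be false.
- *Every message carries a known randomisation probability that the plan wastes.* The text says only that topic choice is based on a probability vector. It does not say that the topic is sampled from it, that the vector is stored, or that every topic keeps a non-zero probability.
- *Making the preparation messages rateable would supply the missing baseline.* It would set ratings before quitting against ratings after quitting, so on its own it leaves the confounding with time in place.

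**Conclusion.** The causal sentence is wrong as written. One cohort compared over time cannot show that later preference is a consequence of training, and the untrained comparator it names is either unrateable or not described. With no learning, 50% dropout and equal rating volume, dropout alone can move precision by 0 to 20 points over the assumed like-rates of 50%/50% to 70%/30%, and it can lower precision if dropouts are the more favourable group. These like-rates are assumptions, since the protocol gives none. They show that the problem can be large, not how large it will be.

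A reader might infer that the whole study fails. It does not: describing precision, time-to-read and engagement over time remains a legitimate aim. What fails is the attribution.

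**What to change.** 1. **Reword.** Replace the causal sentence in App features and clinical integration with a description of change in precision over time. Under Objective quality, do not attribute a month-12 rise to the algorithm. Reconcile these sections with Choosing the message topic and Sending the messages on when learning from ratings begins.
2. **Add a same-patient contrast.** For each later time point, compute the change from month 1 in the patients still rating at that time point, and report it beside the pooled figure. This removes the shift in who contributes. It does not remove novelty, changing interests or selective rating, so the wording must stay descriptive.
3. **Optional and conditional.** If the topic is actually drawn from the probability vector, the vector is logged, and every topic keeps a non-zero probability, add a same-patient, same-period inverse-probability-weighted comparison with uniform topic choice. State that it estimates algorithm selection against uniform choice among rated messages, not trained against untrained. Take any growth over time in the same patients. Report the effective sample size, because precision may be low when the vector is concentrated (70% down to 16% across the example vectors).

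Item 1 costs only text and a more modest claim. Item 2 needs no new data but uses a smaller sample: about 60 of the 120 patients by month 12 at the expected dropout. Item 3 costs analysis work, plus one logged field if the vector is not already stored. The protocol does not say whether it is.
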